#### ESPB group

Patients in ESPB group will be scanned by the linear high-frequency probe firstly placed in sagittal orientation at the middle scapula line. Once the imaging of the 12th rib emerges, T12 spinous process (SP) will be traced by sliding the probe medially and then marked. The probe will be then traced cranially to locate the T10-T11 vertebral. After the same marked method, the probe will be continually moved 3–5 cm laterally and rotated in transverse orientation to identify the muscle layers of erector spinae and transverse processes near the marked site.

After re-confirming the important anatomic structure including lumbar artery under ultrasound scan, a 22-gauge nerve block needle (80 mm, Stimuplex D, B. Braun, Germany) will be inserted in-plane through a medial-lateral direction. Once the needle tip arrives beneath the erector spinae muscle, 3 ml of normal saline will be injected firstly to ensure correct positioning of the needle after aspiration. The prepared study drug will be then injected into this plane with aspiration every 5 ml per injection in case of accidental puncture of vessel or pleura. Successful study drug injection is defined as the appearance of a hypoechoic ellipsoid with well-defined margin beneath erector spinae muscle on ultrasonic view.

#### TPVB group

T10 and T11 vertebral will be located and marked as the same way as that mentioned above in ESPB group. The probe will then be moved 3–5 cm laterally to identify the paravertebral space as the target injection site. After probe being rotated into transverse orientation, a 22-gauge nerve block needle (80 mm, Stimuplex D, B. Braun, Germany) will be inserted using the in-plane technique. Once the needle threads the internal intercostal membrane and arrives in the paravertebral space, 3 ml of normal saline will be injected firstly. If displacement sign of the pleura occurs, the prepared study drug will be then injected into the confirmed paravertebral space. Successful study drug injection is defined as the appearance of pleura displacement sign and hypoechoic ellipsoid in paravertebral space under ultrasonic view.

### Anesthesia management and postoperative analgesia

Intraoperative anesthesia management is performed by an attending anesthesiologist and an assistant; none of whom has knowledge of the allocation. Prednisone methylprednisolone (40 mg) is administered before anesthesia induction, followed by intravenous anesthesia induction with sufentanil (0.1–0.3 μg/kg), propofol (1–2 mg/kg), and rocuronium (0.6 mg/kg). Anesthesia is maintained by intravenous anesthesia combined with or without N_2_O/sevoflurane inhalation to maintain sedation level within the range of 40–60 under bispectral index (BIS) monitor. Opioid analgesics (remifentanil TCI together with sufentanil intermittent administration on demand) are used to maintain analgesia. During the surgery, the fluid volume and infusion speed are adjusted according to hemodynamic monitoring conditions to maintain the blood pressure within 20% of the baseline values. All surgical procedures are performed by fixed surgical team members, and the pneumoperitoneum pressure is often maintained at 12–16 mmHg as usual. After the surgery, standardized patient controlled intravenous analgesia pump is applied for each patient, which was established with 1.25 μg/ml sufentanil and programmed to deliver 4-ml boluses with a lock-out interval of 10 min and no background infusion rate. Patients who are enrolled for this trial will be trained to use a patient controlled intravenous analgesia pump before surgery.

### Endpoints

#### Primary endpoint

The primary outcome in this trial is a joint endpoint of cumulative 24 h opioid consumption after surgery and average pain NRS score at 24 h (valued the average from NRS score at rest and with movement at 24 h) postoperatively.

#### Secondary endpoint

Cumulative opioid consumption at other different times (0.5 h, 2 h, 6 h, 18 h, 24 h and 48 h) after surgery, as well as the time interval to the first bolus demand in PCIA pump, the numbers of required and administered boluses in PCIA pump.Somatic and visceral pain NRS scores both at rest and with movement at preset timepoints (0.5th h, 2nd h, 6th h, 18th h, 24th h, and 48th h) postoperatively.Besides PCIA pump, demand of other rescue analgesic (observed at preset different timepoints, including the time interval to the first rescued analgesic in PACU or in ward).

The other endpoints are defined as follows:
Clinical features of blockage including time-consumption for the intervention, the onset time and time to fixed sensory block, dermatomal distribution of sensory loss, predefined regional distribution of sensory loss, times of puncture, and the adverse events.Quality of recovery scores (QoR-15) (assessed by QoR-15 questionnaire [22]) face-to-face at 24 h after surgery.Sleep quality scores on the nights of the first 2 days after surgery (assessed with NRS scores, 0 = best sleep quality whereas 10 = worst sleep quality).The incidence of postoperative vomiting and nausea score assessed with NRS scores (0 = no nausea whereas 10 = severe nausea) at the following timepoints (0.5th h, 2nd h, 6th h, 18th h, 24th h, and 48th h) postoperatively.The incidence of postoperative moderate to severe pain.Overall incidence of postoperative complication (observation period: until discharge, classified by Clavien-Dindo Classification) [23].Time to first ambulation and diet (observation from the end of surgery).Length of postoperative hospital stay and total length of hospital stay.Anesthesia cost and total hospitalization cost.

### Safety consideration

We will strictly adhere to the steps to minimize the risk of adverse events which might be caused by regional nerve block. First, we will scan eligible patients before the enrolment and exclude those who are difficult for TPVB and ESPB from anatomical point of view. Both blocks will be performed under directly ultrasound guiding by experienced anesthesiologists. Second, the local anesthetic we used for regional block is 1.5 mg/kg ropivacaine (0.4 ml/kg with 0.375% in our study), which has already been proved to be safe in previous studies [24, 25]. Third, regional block will be performed only after intravenous access and standard monitoring are established; therefore, we can detect any adverse events timely. Lastly, participants will be continuously monitored till 24 h after surgery. Researchers will follow-up the participants at preset timepoints after surgery, and all adverse events occurred during this period will be carefully managed and severe adverse events will be reported to the Clinical Research Ethics Committee as soon as possible. If the patient’s harm level meets the insurance claims, payment will be arranged as soon as possible.

### Data collection and management

Baseline data will be collected, including age, gender, birth date, education years, weight, and height. Co-morbidities as well as important laboratory tests and instrumental examination will be documented. Preoperative recent sleep quality will be assessed with Pittsburgh Sleep Quality Index (PSQI) [26]. Intraoperative data, including duration of anesthesia and surgery, surgical information, and anesthesia medication including opioid consumption and fluid balance will be documented. Pneumoperitoneum pressure will be documented as an average throughout the operation. Outcome data will be evaluated and recorded according to the follow-up plan to ensure all timepoints data are noted.

Based on the original observation records of the participants, the data are collected into the case report forms timely, completely, and correctly. All data will be kept confidentially. Data entry will be performed in a double-input and double-check way with the REDCap (Research Electronic Data Capture) database system developed by the Vanderbilt University. The data will be monitored and sampled regularly in the trial by the Clinical Research Ethics Committee, and the database will be locked after the electronic data is checked. After data entry and verification as required are completed, the case report forms will be filed in numbered order and kept in a specific filing cabinet. We have no plan in interim analysis until the target sample size is achieved.

## Statistical analysis

### Sample size calculation

The primary endpoint of this non-inferiority trial is the joint of cumulative 24 h opioid consumption after surgery and average pain NRS score at 24 h postoperatively.

In a pilot investigation of our patients, the mean (± standard deviation) of the cumulative 24 h opioid (sufentanil) consumption after laparoscopic nephroureterectomy was about 25.7 (± 2.0) μg with TPVB and 35 (± 14.0) μg with non-block respectively (data were unpublished yet). The non-inferiority margin was set as 5 (unit: μg; clinical practice treated it as an acceptable difference) [27]. With a significance level of *α* = 0.05 and a power of 1-β = 90%, the sample size required to detect difference was 77 patients in each group.

A 1–1.3 point difference in pain NRS scores is usually considered as acceptable subjective pain discrimination [28]. When the standard deviation of the pain NRS score was assumed as 2.5 and the non-inferiority margin of NRS was 1 score [29], 70 samples were estimated per group.

Hence, the greater sample calculated above was 77 participants per group. Considering a dropout rate of 5% and technique failure rate of 3%, we finally planned to enroll 83 participants per group (a total of 166 participants). The sample size was estimated by the PASS software (version 11.0; NCSS PASS, UT, USA).

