**Methods and analysis:**

This prospective, randomized, double-blinded, non-inferiority trial will enroll 166 patients undergoing laparoscopic nephroureterectomy. Participants will be randomly assigned 1:1 into receiving ESPB or TPVB before surgery. Both ultrasound-guided ESPB and TPVB will be performed with an injection of 0.375% ropivacaine 0.4 ml/kg before anesthesia induction. Standardized patients controlled intravenous analgesia (PCIA) will be applied for each patient. The primary endpoint is the joint of cumulative 24 h opioid (sufentanil) consumption and average pain score via numeric rating scale (NRS) at 24 h after surgery. Secondary endpoints include rescued analgesic demand, cumulative opioid consumption, and pain NRS scores at different preset timepoints within 48 h after surgery. Other predefined outcomes include clinical features of blockage, quality of recovery, subjective sleep quality, time to ambulation and diet, and adverse events, as well as length of stay in hospital and anesthesia cost.

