### Primary endpoint

#### Non-inferiority

Cumulative 24 h opioid consumption and average pain NRS score at 24 h after surgery is the primary joint endpoint, which will be analyzed by “joint hypothesis test.” In this analysis, the intervention group could be considered effective as long as either of the two endpoints is non-inferior. The confidence interval method will be used to perform the non-inferiority test, and the result will be expressed as effect size (difference) (95% CI). If the effect size upper limit of the one-side 95% CI is smaller than 5 in cumulative 24 h opioid consumption, we will conclude that ESPB is non-inferiority to TPVB; in addition, when average pain NRS scores at 24 h after surgery is smaller than 1, ESPB group will be also considered non-inferiority.

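### The NRS sample size of 70 per group does not follow from SD 2.5 and margin 1: these inputs need 108, so 77 is not the greater requirement

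*Protocol article*

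**What the plan says.** The Protocol article, Sample size calculation, sizes the two components of the joint primary endpoint one after the other. Alpha and power are printed once, in the opioid paragraph: "With a significance level of *α* = 0.05 and a power of 1-β = 90" per cent, leading to 77 per group against a 5 μg margin.

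The NRS paragraph gives a standard deviation, a margin and a result in one sentence, with the SD "assumed as 2.5 and the non-inferiority margin of NRS was 1 score [29], 70 samples were estimated per group". It states no separate alpha or power and no expected difference between the groups.

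The two results are then compared: "Hence, the greater sample calculated above was 77 participants per group". After allowance for 5% dropout and 3% technique failure, this becomes 83 per group, and the Abstract accordingly "will enroll 166 patients undergoing laparoscopic nephroureterectomy".

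The Non-inferiority section fixes the sidedness of the test, at least for opioid use: "If the effect size upper limit of the one-side 95% CI is smaller than 5 in cumulative 24 h opioid consumption". It applies a limit of 1 point to the NRS score, the same as the planning margin. It also treats ESPB as effective if either component is non-inferior.

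**The concern.** The ratio of SD to margin is 2.5, and at 90% power and the usual error rates that calls for well over 70 per group. If 70 is wrong, so is the comparison that makes 77 the larger figure, and the trial size is then not shown to cover the pain component. A reader of the results would take an inconclusive NRS comparison as coming from a test with 90% power, when on the printed inputs it had less. The article calls opioid use and pain score equally important, so the planning figures for pain should be right in their own terms.

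**Working it through.** **Inputs**

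- SD 2.5 points and margin 1 point (NRS paragraph of Sample size calculation).
- Alpha 0.05 and power 90% (opioid paragraph of the same section). Carrying them over to NRS is an inference. It is the natural one, because the two sample sizes are compared directly.
- One-sided alpha 0.05, from the one-sided 95% limit in the Non-inferiority section. This reading needs the fewer patients; one-sided 0.025 is shown alongside.
- True difference 0. The article states no other value.
- 1:1 allocation (Randomization).

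**Required n per group**

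n = 2 × SD² × (z₁₋α + z₁₋β)² / margin²

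- One-sided 0.05: 2 × 2.5² × (1.645 + 1.282)² / 1² = 12.5 × 8.567 = 107.1, so 108. An exact search with the noncentral t distribution also gives 108.
- One-sided 0.025: 12.5 × (1.960 + 1.282)² = 131.4, so 132; exact t gives 133.

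**Attempts to reproduce 70** (one-sided 0.05 unless stated)

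| Inputs | n per group | Stated in the article? |
|---|---|---|
| SD 2.5, margin 1, 90% power | 108 | yes, with alpha and power carried over |
| SD 2.5, margin 1, 85% power | 91 (t) | no |
| SD 2.5, margin 1, 80% power | 78 | no |
| SD 2.5, margin 1, 85% power, one-sided 0.10 | 68 | no |
| SD 2.5, margin 1.3, 90% power | 65 (t) | no; 1.3 is only the top of the quoted range of acceptable differences |
| SD 2.5, margin 1.25, 90% power | 69; 70 by t | no |
| SD 2.0, margin 1, 90% power | 69; 70 by t | no |
| SD 2.5, margin 1, true difference −0.25 (favouring ESPB), 90% power | 69; 70 by t | no |
| 2.5 as the SD of each single score, rest–movement correlation 0.3, 90% power | 70; 71 by t | no |

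In the last row, the SD of the average is 2.5 × √((1 + 0.3)/2) = 2.02. At a correlation of 0.5 the requirement is already 81.

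Dropping to 80% power does not rescue the comparison either: 78 exceeds both 70 and 77.

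**NRS power at the planned sizes** (SD 2.5, margin 1, true difference 0, noncentral t)

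| n per group | one-sided 0.05 | one-sided 0.025 |
|---|---|---|
| 70 | 76% | 65% |
| 77 | 80% | 69% |
| 83 | 82% | 73% |

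**Gap.** 108 − 77 = 31 evaluable patients per group. With the article's combined 8% loss, 108 / 0.92 = 117.4, so 118 enrolled per group against 83 planned.

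**Effect on the planned decision rule.** When either component suffices, power is at least that of the stronger component. If opioid use has its stated 90% and NRS 80%, and the two were independent, power for the rule would be 1 − 0.10 × 0.20 = 98%. With any dependence it cannot be below 90%.

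**The case against.** The strongest reply is that the article never states 90% power for NRS: alpha and power are printed only in the opioid sentence. That is so, and the carry-over must be labelled as an inference. It does not save the figure, because even 80% power at the stated SD and margin needs 78, and the only alpha and power pair tried that comes near 70 (one-sided 0.10 with 85% power) contradicts what is printed.

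A second reply is that an unstated input may lie behind 70: a small true advantage for ESPB, or an SD meant for a single score when the endpoint averages rest and movement. Both are possible, as the table shows, and so SD 2.0 is only one candidate source. As neither is stated, the printed inputs and the printed result still disagree.

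A third reply concerns consequence, and it stands. The Non-inferiority section lets either component establish non-inferiority. A reader might infer that the primary analysis is underpowered as a whole; the documents do not support that, for the reason shown at the end of the working.

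A reader might also infer that NRS would be the limiting component if both had to be met. That cannot be established. The SD behind the opioid 77 is not given. The figure implies about 10.5 μg, while the SDs printed are 2.0 (TPVB) and 14.0 (no block). At SD 14 and margin 5 the opioid component would need 135 per group, more than 108; at SD 10 it would need 70.

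**Conclusion.** The point holds. On the stated SD and margin, 70 per group is wrong and 77 is not the greater of the two requirements. The NRS requirement is 108 per group at one-sided 0.05 and 133 at one-sided 0.025. With 77 evaluable per group, the NRS comparison has about 80% power (82% with all 83), or 69% and 73% at one-sided 0.025. These figures assume a zero true difference and the carried-over alpha and 90% power target.

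The article does not show whether an input was misprinted or the result miscalculated. Under the plan as written, the harm is a false planning statement and a pain comparison weaker than the text implies, not a failure of the either-component rule to reach 90% power.

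**What to change.** Reconcile the SD, margin and n for NRS in Sample size calculation.

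- If other inputs produced 70 (for example SD 2.0, or a non-zero true difference), print and justify them.
- If SD 2.5 and margin 1 stand, replace 70 with 108. Replace the sentence that calls 77 the greater sample with one saying that 77 evaluable (83 enrolled) per group rests on the opioid component. Add that 77 per group gives about 80% NRS power at one-sided 5%, and that this is accepted without enlarging the trial.

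In either case, state the alpha, its sidedness and the power for the NRS calculation itself.

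The cost is a few corrected sentences; the total of 166 can stay. The second option does openly accept the lower NRS power. Keeping 90% by the article's own larger-of-two rule would instead mean about 118 enrolled per group.

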### Endpoints analysis

Baseline characteristic will be compared according the data distribution and type. In addition to graph method for qualitative analysis, Shapiro-Wilk test will be also used for quantitative analysis in review of data distribution. Continuous data with normal or approximate normal distribution will be expressed as mean ± standard deviation, while continuous data with non-normal distribution is expressed as median (interquartile, IQR). Continuous data will be tested by independent sample *t* test or Mann-Whitney *U* test according to data distribution. Categorical data will be expressed as numbers (percentages) and tested by chi-square test/Fisher’s exact test. Time-to-event data will be analyzed by the Kaplan-Meier estimator, with the difference between groups tested by the log-rank method. Two-tailed *p* values of less than 0.05 are regarded as statistically significant. All statistical analyses are performed with the SPSS 25.0 statistical package (IBM SPSS Inc., Chicago, IL, USA).

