## Strengths and limitations of this study

Our study is the first trial in non-inferiority, double-blinded design of comparing ESPB with TPVB for analgesia in laparoscopic nephroureterectomy.The primary outcome in our study is set as a joint endpoint of opioid consumption and pain NRS scores, both of which are deemed equal important in evaluating pain control.This study will investigate not only erector spinae plane block efficacy of analgesia, quality of postoperative recovery as usual, but also its clinical features of blockage.The relatively small sample size may limit to discriminate the safety consideration between the two blocks technique.A single-center trial design may limit its universality.

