Compared with TPVB, ESPB has the following advantages. First, the dermatomal distribution of sensory loss is extensive, which covers the area ranging from the ipsilateral parasternal to the midline of the lower back in a single shot block. It has been reported that ESPB performed at T5 level can give a sensory loss dermatome from T2 to T9 [6, 17], while local anesthetic solution spreading cranially to the upper thoracic level and caudally as far as the L2-L3 level is founded in ESPB performed at T7 level [18]. Second, regarding to safety, ESPB is conducted in shallow layer and far away from important organs and blood vessels; therefore, the risk of pneumothorax [19, 20], hematoma, nerve injury, and other complications involves less than TPVB theoretically. Finally, when it comes to the simplicity and convenience, the ultrasound imaging features of muscle layers and transverse processes are easy to identify and locate [21].

Although studies have shown that ESPB has a better analgesic effect comparing with traditional opioid intravenous analgesia, there is still a lack of evidence in direct comparing the analgesic efficacy between ESPB and TPVB in urological surgery. Besides, most of previous studies just chose a single endpoint for postoperative pain evaluation and the follow-up period is often limited within 24 h after surgery. Our study is the first trial in non-inferiority design in comparing of ESPB and TPVB with a 48 h follow-up after surgery in patient undergoing laparoscopic nephroureterectomy, and the primary outcome is a joint endpoint of opioid consumption and pain NRS (numeric rating scale) scores.

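### If costs are right-skewed, the general distribution rule leaves the two cost outcomes without an estimate of the difference in mean cost per patient; adding one is a cheap improvement

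*Protocol article*

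**What the plan says.** The Secondary endpoint section of the protocol article closes its list of other outcomes with "Anesthesia cost and total hospitalization cost". The abstract names anesthesia cost alone.

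Under Statistical analysis, the primary and secondary endpoint subsections give specific methods only for opioid consumption and pain scores. Costs therefore fall under the general rule in Endpoints analysis:

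- Distribution is judged by graphs, and "Shapiro-Wilk test will be also used for quantitative analysis in review of data distribution".
- Normal or approximately normal data are summarised by mean and standard deviation; otherwise "continuous data with non-normal distribution is expressed as median (interquartile, IQR").
- The choice of test follows the same judgement: "Continuous data will be tested by independent sample *t* test or Mann-Whitney *U* test according to data distribution".
- The threshold is the usual one: "Two-tailed *p* values of less than 0.05 are regarded as statistically significant".

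The article states no mean cost difference and no confidence interval for cost. It also states no cost hypothesis, no payer perspective and no expected shape for the cost data.

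**The concern.** For most uses of a cost comparison the quantity wanted is the average cost per patient, because total spend is the number of patients times the mean. A median does not give total spend, and a rank test does not estimate a difference in means. The rule also lets a normality check on the trial's own data decide which quantity is reported, so that quantity is not fixed in advance.

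Total hospitalization cost is where this bites. A small number of long or complicated stays can carry much of the difference in spend while leaving the middle of the distribution almost where it was. Followed as written, the trial could report similar costs when average costs differ. It could also report a difference when average costs are the same.

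**Working it through.** **Inputs from the document.** 83 per group (Sample size calculation: "we finally planned to enroll 83 participants per group (a total of 166 participants")) and two-sided 0.05 (Endpoints analysis). The document has no cost figure to reproduce.

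**Assumed inputs.** The cost of an uncomplicated stay is lognormal with mean 1 and coefficient of variation (CV) 0.25. A complicated stay costs *m* times as much. Complication rates are *p* in each arm. None of these stands in the document.

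**Step 1: true means.** Mean cost = 1 + *p*(*m* − 1). With *m* = 3 and rates of 2% (ESPB) and 8% (TPVB):

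- ESPB: 1 + 0.02 × 2 = 1.04
- TPVB: 1 + 0.08 × 2 = 1.16
- Difference (TPVB − ESPB): 0.12

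**Step 2: what each summary shows.** In simulated trials of this scenario the mean difference averaged 0.118 and the median difference 0.020. The median therefore showed 0.020/0.118, about 17%, of the difference in spend. A second cost model was also tried: base cost 100 with CV 0.2 to 0.5, plus a gamma-distributed extra cost averaging 200 or 400 in 0–2% versus 3–10% of patients. There the median showed about 7% to 28% of the true mean difference.

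**Step 3: which route the rule takes.** Shapiro-Wilk rejected normality in at least one arm in over 99% of trials in the first three scenarios of the table, and in 96–100% under the second cost model. With lognormal costs and no complications at all it rejected in 87%.

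**Step 4: rejection rates at two-sided 0.05, 83 per arm.**

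| Assumed scenario (ESPB vs TPVB) | True mean difference (absolute) | Mann-Whitney | Welch |
|---|---|---|---|
| 2% vs 8%, *m* = 3 | 0.12 | 9.9% | 29.2% |
| 1% vs 6%, *m* = 2 | 0.05 | 7.2% | 14.5% |
| 2% vs 10%, *m* = 5 | 0.32 | 13.0% | 53.7% |
| 1% vs 3%, *m* = 3 | 0.04 | 5.7% | 8.2% |
| 0.5% vs 2%, *m* = 3 | 0.03 | 5.4% | 6.8% |
| 5% in both, *m* = 3, uniform 10% cost shift | 0.11 | 58% | 26% |
| 2% in both, *m* = 5, uniform 10% cost shift | 0.108 | 64% | 23% |

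Neither test is better throughout. They respond to different kinds of difference.

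**Step 5: means nearly equal.** Let the typical ESPB stay cost 12% more, with 2% versus 8% complications and *m* = 3. The means are 1.12 × 1.04 = 1.165 and 1.16, practically the same. Mann-Whitney rejected in 46% to 48% of trials over two runs.

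**Step 6: is a comparison of means valid at this size?** With 2% complications in both arms and *m* = 3, Welch rejected in 5.1% of trials, so skewness of this degree does not upset its error rate.

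**Step 7: how wide would the interval be?** In the Step 1 scenario, variance = 1.0625 × (1 + 8*p*) − mean².

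- TPVB: 1.0625 × 1.64 − 1.3456 = 0.397
- ESPB: 1.0625 × 1.16 − 1.0816 = 0.151
- Standard error: √((0.397 + 0.151)/83) = 0.081
- 95% half-width: 1.96 × 0.081 ≈ 0.16, against a true difference of 0.12

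**The case against.** The strongest reply is that median (IQR) with Mann-Whitney is a conventional general rule. Cost is the last of the other outcomes and is not among the aims in Study objectives, and a cost-specific estimator may sit in an analysis plan that is not shown. Much of this stands: the rule is neither an error nor a contradiction. What remains is that the article does state a method covering costs, and that method does not yield a mean difference once the data are judged non-normal.

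Four stronger readings are tempting, and the document does not support them.

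- *ESPB is expected to save money.* The Introduction says only that "hematoma, nerve injury, and other complications involves less than TPVB theoretically". It makes no link to cost.
- *The rule hides expensive complications.* It does not. Block-related adverse events, complications to discharge graded by Clavien-Dindo, and length of stay are separate outcomes, and the categorical ones get counts and percentages.
- *Comparing means would rescue power.* The advantage in the first rows of the table comes from assumed rates and multipliers. It nearly vanishes for smaller gaps and reverses for a uniform cost shift. Even at 2% versus 8%, Welch misses the difference in about 71% of trials. The authors themselves concede that "The relatively small sample size may limit to discriminate the safety consideration between the two blocks technique".
- *Both costs will certainly go to medians.* Graphs are weighed alongside the test, and approximately normal data keep the mean. Right-skew is an expectation, and anesthesia cost need not contain the cost of a complicated stay.

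**Conclusion.** The point holds as one about what is estimated. The general distribution rule is the only analysis stated for the two cost outcomes, and right-skewed costs would very probably be reduced by it to a median and a rank test. In the scenarios examined for median size, the median carried roughly 7% to 28% of the true mean difference, and Mann-Whitney could reject in nearly half of trials with practically equal means. These sizes rest wholly on assumed cost shapes, complication rates and cost multipliers, and they concern mainly total hospitalization cost. The non-inferiority conclusion is untouched. This is a cheap improvement, not a defect that threatens the trial.

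**What to change.** Add one sentence to Endpoints analysis. For both cost outcomes, whatever the Shapiro-Wilk result, the main comparison is the arithmetic mean cost per arm and the ESPB minus TPVB mean difference with a bootstrap (or Welch) 95% CI; the median (IQR) and Mann-Whitney result are supplementary description.

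This needs no new data and changes no other analysis. The price is an interval that may be wide (Step 7) and a main comparison that is less sensitive than Mann-Whitney to a uniform cost shift, which is a reason to keep the rank test alongside it.
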